### Recruitment and consent

Care homes will be recruited in one region in the north-east of England from local care home networks and organizations. Care homes will be screened for initial eligibility via publicly available information. Initially, 8 care homes will be sent recruitment information by email. This will be followed up by a phone/video-conferencing call to confirm interest and to complete initial eligibility screening. A mutually convenient time to visit the care home will then be scheduled to determine full eligibility and complete the recruitment process (i.e., written agreement at the care home level and appropriate management permissions). Additional care homes will be approached if recruitment rates are not achieved with the first 8 care homes.

#### Residents

Anonymous resident screening will take place by the care home manager and a researcher to determine eligibility for approach. An initial discussion about capacity to give informed consent will take place at this point, with the consent process followed for a personal consultee for residents who would be unable to give informed consent to take part in the research. A member of care home staff will then approach eligible residents to ask if they are willing to talk to the researcher. The researcher will explain the study to the resident using the participant information sheet. Consent will be sought for proxy completion of outcome measures, access to their care plan/medical records, and for completion of the COG-D assessments. Resident consent procedures will adhere to the Mental Capacity Act 2005 [19]. Those who can give informed consent will sign or make a mark on the trial consent form. Where a resident is unable to sign, or make a mark, they will be asked to indicate their consent verbally (witnessed by an independent observer). If there is doubt about mental capacity of eligible residents a mental capacity assessment will be completed by the researcher. Where a resident is judged to lack capacity, a personal consultee (usually a family member or friend) will be appointed to provide advice on their wishes. Where no personal consultee is available, a nominated consultee from the care home (a member of staff not involved directly with the study) will be appointed to provide this advice. Personal consultees will be approached in the care home by staff who will introduce the researcher, or by letter/email (sent by the care home manager). In case residents lose capacity during the trial, appropriate guidance on consent in the light of changed capacity will be followed [19], with a personal or nominated consultee appointed to provide advice on the person’s continued participation. At each COG-D assessment session, the resident’s willingness to continue, once initial consent has been secured, will be ascertained.

#### Staff

Short information leaflets about the study will be circulated and placed at convenient locations in the care home. Researchers will approach staff to explain the aim of the study and staff involvement. Interested staff will be provided with the Participant Information Sheet (PIS) and a Consent Form for participation in the study. Researchers will follow up with staff to obtain written consent. A separate consent form is attached to the paper version of the anonymous Staff Questionnaire with candidate outcome measures, and the online version of the Staff Questionnaire is preceded by an eConsent Form.

### Recruitment for interviews/focus groups

#### Residents

Staff and/or the researcher will approach residents they feel may be most able to provide their views on COG-D and its impact (e.g., residents who have resided in the home throughout the study and may be more likely to recall the COG-D assessments). Resident interviews will be brief, using a conversational style and will follow a standardized interview schedule. A sample of up to 2–3 eligible staff will be approached to take part in a focus group and will be provided the PIS and the Consent Form. Relatives or friends eligible to participate in interviews will be identified by the care home manager in discussion with the researcher. Eligible relatives/friends will be approached by the researcher to take part in a focus group held in the care home, at the University of Lincoln, or (in the case of interviews) via an individual telephone/video conferencing interview.

### Assignment of intervention

Randomization of care homes will take place after collection of baseline measures. A web-based randomization system built in the REDCap Cloud electronic data capture system (EDC) will be provided by the Hull Health Trials Unit (HHTU). Randomization by minimization will be undertaken at care home level in 1:1 ratio and stratified by site size (large > 40 beds–small < 40 beds). Each care home will be randomized centrally and dynamically after collection of baseline data is completed. A separate randomization strategy SOP with details on randomization by minimization will be produced and implemented.

To prevent experimenter bias during collection of post-intervention candidate outcome measures (6 and 9 months post-randomization), one of the three trial-specific researchers will be blinded for the condition of each care home (UC or UC + COG-D). Care homes allocated to the COG-D intervention arm will be reminded to remove any references to COG-D (e.g., posters, leaflets, Daisies) in areas where researchers meet care staff who provide proxy data for residents at 6 and 9 months post-randomization. If unblinding happens by accident, then this will be reported to the CI. The feasibility and effectiveness of this approach will be considered in the design of the future planned RCT.

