### Outcomes

Primary outcome of this study are the feasibility outcomes, including recruitment and retention rate, acceptability, fidelity and adherence to COG-D intervention protocol, acceptability and data completion rates, and feasibility of health economic assessment. Key feasibility criteria a presented in Table 2. Secondary outcomes are the candidate outcomes for a definitive cRCT (see Table 3).

**Table 2 Tab2:** Key progression criteria

*Key progression criteria*	
Percentage recruited residents	*Green > 60%, amber 40–60%, red < 40%*
Percentage of recruited residents for completion of COG-D and COG-D re-assessment	*Green > 60%, amber 40–60%, red < 39; re-assessment: 70% of these estimates*
Percentage of recruited staff completing basic training	*Green > 60%, amber: 40–60%, red < 40%*
Percentage of recruited senior staff completing advanced training	*Green > 75%, amber 60–74%, red < 60%*

**Table 3 Tab3:** Candidate outcome measures

Outcome measures	Outcome	Description
*Residents*		
Cohen-Mansfield Agitation Inventory CMAI [23, 24]	Agitation	Lists 29 agitated behaviors. By proxy rating of frequency of occurrence in the previous 2 weeks, ranging from never (1) to several times an hour (7). Scores range from 29 to 203. A high score indicates high levels of agitation.
Quality of Life in late-stage Dementia scale QUALID [25]	Quality of Life	By proxy ratings (1 to 5) of 11 behaviors. Scores range from 11 to 55; low scores indicate higher levels of quality of life.
Bristol Activities of Daily Living Scale BADLS [26]	Independence in daily activities	By proxy rating (1–5) of average ability on 20 activities in the preceding 2 weeks. Scores range from 20 to 100. Low scores indicate higher levels of independence.
EQ-5D-5L: Instrument to describe and value health [27]	Health-related quality of life	By proxy rating (1–5) of health-related quality of life in five domains. Scores range from 20 to 100. A low score indicate a higher level of health-related quality of life.
Functional Assessment Staging of Alzheimer’s disease FAST [20]	Estimate of dementia stage	Functional scale designed to evaluate people at the more moderate-severe stages of dementia. The scale has seven stages, the highest rating (7) indicates ‘severe dementia’. Ratings are guided by functional milestones.
*Staff*		

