#### Feasibility outcomes

Recruitment and retention of care homes, residents, and care-staff in both intervention and control conditions will be calculated to inform the number of care homes needed to achieve the target sample size for a future definitive trial. Acceptability, fidelity, and adherence to COG-D intervention protocol will be evaluated with completion rates for staff training and COG-D assessments, use and display of Daisies and revisions to care-plan based on COG-D assessments.

Feasibility of a Health Economic assessment will be explored in the ability to collect the data required (COG-D use, resource use, health and quality of life of residents) to undertake a cost-effectiveness analysis in the definitive trial and estimate potential costs and health benefits of the intervention.

Demographic data for residents (age, ethnicity, length of time in care home, gender, dementia diagnosis) will be collected from care plans. For staff, data will be obtained as part of the anonymous staff questionnaire (further training completed, duration of employment at care home) or in a short questionnaire preceding the staff training (role in care home, ethnicity (to explore diversity), age category, gender).

Candidate outcome measures for residents (by proxy) will be collected in interviews with researchers and staff outcomes are collected in the anonymous staff questionnaire (self-completed). Data completion rates of the candidate outcome measures (at each time point) will be calculated to determine which is the most appropriate primary outcome, agree other study measures and inform sample size calculation for the definitive trial.

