### Data analysis

Analysis and reporting will adhere to CONSORT 2010 guidelines extension for feasibility trials [22]. A CONSORT flow diagram will be used to display data completeness and resident throughput from eligibility screening, invitation, study acceptance, and final follow-up visit. Feasibility figures on recruitment and retention, COG-D completion, adherence to COG-D implementation protocol, outcome completion rate, and adverse event will be reported and checked against the pre-defined progression criteria.

Signals of efficacy will be analysed in resident and staff candidate outcome measures. Proposed outcome measures (residents: CMAI [23, 24], QUALID [25], BADLS [26], FAST [20], and EQ-5D-5L [27]; care-staff: SCIDS [28], CBI [29], and COG-DQ [15]) will be summarized at baseline, 6-month, and 9-month follow-up. Calculated effect sizes of candidate outcome measures (CMAI, QUALID, and the BADLS), and their corresponding intraclass correlation coefficients (ICCs), will be employed to establish the primary endpoint and sample size for the future definitive cRCT. The calculated completion rates of study measures and questionnaires will be utilized, with their burden and acceptability, to inform the choice of study outcomes for a future large-scale cRCT.

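### Observed effect sizes from unblinded staff ratings in 8 to 10 homes should not set the definitive trial's primary endpoint and sample size

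*Protocol article*

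**What the plan says.** All places are in the protocol article.

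- **Source of the ratings.** Table 3 (Outcomes) describes CMAI as "By proxy rating of frequency of occurrence in the previous 2 weeks" and QUALID as "By proxy ratings (1 to 5) of 11 behaviors"; BADLS and EQ-5D-5L are proxy-rated too. Under Feasibility outcomes: "Candidate outcome measures for residents (by proxy) will be collected in interviews with researchers". Assignment of intervention identifies the proxies as care staff, since COG-D material is to be removed "in areas where researchers meet care staff who provide proxy data for residents at 6 and 9 months post-randomization".
- **Who is blinded.** The same section states that "one of the three trial-specific researchers will be blinded" to each home's condition. It gives the purpose as avoiding experimenter bias and says the approach will be reviewed when the future trial is designed.
- **What staff know.** In intervention homes, basic training is aimed at all care staff who will use the Daisy (Staff training). Daisies and posters are displayed and weekly huddles are held (Use of COG-D in daily care practice).
- **Use of the results.** Data analysis says that the effect sizes of CMAI, QUALID and BADLS and their ICCs "will be employed to establish the primary endpoint and sample size for the future definitive cRCT". Item 4 of the primary objective says the same of effect sizes. Completion rates, burden and acceptability are named as further inputs to the choice of outcomes (Feasibility outcomes; Data analysis).

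**The concern.** The person who produces each resident's score is a staff informant, not the interviewer. Blinding the interviewer leaves the informant's knowledge of the arm untouched. COG-D is also meant to change how staff see residents: the logic model in the Background expects it to help them identify needs that arise from cognitive problems. A difference between arms in proxy scores can therefore reflect changed behaviour, changed perception or expectation, and this design cannot separate them.

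That would be acceptable if the effect sizes were only described. The plan instead gives them two jobs. Comparing observed effects across three scales to help pick the endpoint partly ranks the scales by how readily informants' ratings shift. Putting the observed effect into the sample size passes on both the possible bias and the sampling error. The harm would fall on the definitive trial, through a poorly chosen endpoint or the wrong number of homes.

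**Working it through.** **1. The plan's own figures.** From Sample size: 70 evaluable residents and 30% loss give 70 / (1 − 0.30) = 100. The half-width on retention is 1.96 × √(0.7 × 0.3 / 100) = 0.0898, the stated ±9%, with no allowance for clustering. Both reproduce. This precision is for retention; the article gives none for an effect size.

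**2. Precision of a standardised effect.**
Inputs: 35 residents per arm (Sample size); 8 to 10 homes at 1:1, so k = 4 or 5 homes per arm (Study setting; Trial design). The ICC is not given, so 0.05 is assumed, with 0 and 0.10 as a range.
Formulas: design effect DE = 1 + (35/k − 1) × ICC; SE = √(2/35 × DE); half-width = t(2k − 2) × SE, where t(6) = 2.447 and t(8) = 2.306.

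| ICC (assumed) | k | DE | SE | 95% half-width (SD) |
|---|---|---|---|---|
| 0 | 4 | 1.00 | 0.24 | 0.58 |
| 0 | 5 | 1.00 | 0.24 | 0.55 |
| 0.05 | 4 | 1.39 | 0.28 | 0.69 |
| 0.05 | 5 | 1.30 | 0.27 | 0.63 |
| 0.10 | 4 | 1.78 | 0.32 | 0.78 |
| 0.10 | 5 | 1.60 | 0.30 | 0.70 |

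With the normal quantile 1.96 in place of t, the range is 0.47 (ICC 0) to 0.62 (ICC 0.10, k = 4). On either basis, an observed 0.3 SD would have an interval that includes zero and effects well above 0.7.

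**3. What a rating bias would do to the planned size (illustration only).** The true effects and biases are assumed; the documents give neither. Two-sided 5% test, 80% power, SD 1, before any design effect: n per arm = 2 × (1.96 + 0.84)² / d², rounded up. This gives 393 at d = 0.2, 175 at 0.3, 99 at 0.4, 63 at 0.5 and 44 at 0.6. True power is Φ(d_true × √(n/2) − 1.96).

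| True effect | Bias +0.1: n per arm, true power | Bias +0.2: n per arm, true power |
|---|---|---|
| 0.2 | 175, 46% | 99, 29% |
| 0.3 | 99, 56% | 63, 39% |
| 0.4 | 63, 61% | 44, 47% |

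In the other direction, a bias that lowered a true 0.3 to an observed 0.2 would lead to 393 per arm where 175 suffice, or 393 / 175 = 2.2 times the size needed.

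**4. Which inputs are less exposed.** A rating shift that is the same for everyone in one arm changes the difference between arms. It leaves the within-arm SD, the ICC within arms, completion and retention unchanged.

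**The case against.** The strongest reply is that the article is more modest than this point may suggest, and much of that reply stands.

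- A reader might infer that the article presents the resident outcomes as blinded. It does not. Its stated aim is "To prevent experimenter bias during collection of post-intervention candidate outcome measures (6 and 9 months post-randomization"), it blinds a researcher, and it promises to review the approach. The blinding statement is not wrong.
- A reader might infer that the endpoint will be picked on observed effect alone. ICC, completion, burden and acceptability are already named, and completion rates are also to inform the sample size. The change needed is narrower: take the effect size out and add an SD and a minimally important difference.
- A reader might infer that every informant delivers COG-D. The article does not say that a given resident's informant was trained. Agency and bank staff are eligible, and training completion is itself a progression criterion. Knowledge of the arm is a safe inference; personal delivery is not.
- A reader might infer that bias will inflate the effect and undersize the trial. The documents do not fix the direction. Staff who notice more difficulties could report more dependence or distress, which would shrink the effect.
- The wide interval is not evidence of bias. A shift between arms could not be recognised at any sample size without an unbiased comparator. Imprecision is a separate weakness of the same input.

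The article does describe the measures as secondary and speaks of signals of efficacy. That does not answer the point, because item 4 of the primary objective and Data analysis go further and make the effect sizes a design input, with no caveat about the informants.

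**Conclusion.** The point holds for one stated rule: using the observed effects on CMAI, QUALID and BADLS to establish the future endpoint and sample size. Two facts in the article make this an unreliable input. The ratings come from staff who can be taken to know the arm, and 35 residents per arm in 4 or 5 homes give a 95% half-width of about 0.63 to 0.69 SD at an assumed ICC of 0.05 (0.55 to 0.78 for ICC 0 to 0.10).

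The true power of 56% or 39% rests on an assumed true effect of 0.3 SD and an assumed inflation of 0.1 or 0.2. It shows how sensitive the plan would be and does not predict what will happen. No stated number in the article is wrong, and the feasibility outcomes are unaffected. The rule should be changed, because the harm would fall on the definitive trial and the remedy is cheap.

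**What to change.** Change item 4 of the primary objective and Data analysis together, since editing only one would make them disagree.

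1. Remove the observed effect size as a basis for the endpoint and the sample size.
2. Choose the endpoint on completion, burden, acceptability, SD and ICC.
3. Base the sample size on a minimally important difference for the chosen scale, with the pilot SD, ICC and retention. An ICC from 8 to 10 homes will itself be imprecise, so use a range of values.
4. Report effect sizes with cluster-adjusted confidence intervals, described as signals from unblinded informants. The secondary objective on signals of efficacy can stay.

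The cost is wording, including one item of the primary objective, plus the work of justifying a minimally important difference, which the article does not give. The downside is that the observed effect no longer feeds the sample size. No extra raters are needed. Saying in Assignment of intervention that informants are unblinded would be a useful clarification, but the fix does not depend on it.

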##### Use of COG-D in daily care practice

The Daisies without labels will be placed in locations where they are most useful (e.g., in residents’ rooms) and Daisies with labels are included in the care-plans. Recruited staff will be provided with the Petal-By-Petal Guide. Larger posters of the Cognitive Daisy (not resident-specific version) will be displayed in dining areas and in communal spaces where scheduled activities take place.

To support staff and to monitor use of resident Daisies, a range of activities will be arranged during this phase of the intervention: (1) weekly guided ‘huddles’ [17] and fortnightly virtual COG-D drop-in sessions for staff to ask questions about the use of Cognitive Daisies, share good practice and to monitor use; (2) care plan review meetings (after the initial and the second COG-D assessment period) to discuss how Daisies can be used to update care-plans; (3) monthly COG-D Assessor drop-in sessions (senior staff) to ask questions and for sharing of good practice; (4) monthly newsletters to update intervention arm care homes about the progress of the COG-D project and to summarize suggestions on the use of COG-D in practice, based on the huddle and drop-in session discussions. Control homes will receive the newsletter content related to general study progress without any COG-D specific content.

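### The plan will judge its blinding approach, but the only data it names are reported accidents, and its removal rule may overlap with Daisy display as an adherence measure

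*Protocol article*

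**What the plan says.** All of the masking text is in the protocol article under Assignment of intervention. One of the three trial researchers is masked to each home's arm for the follow-up outcomes. The protective step reads: "Care homes allocated to the COG-D intervention arm will be reminded to remove any references to COG-D (e.g., posters, leaflets, Daisies) in areas". The same sentence limits this to places "in areas where researchers meet care staff who provide proxy data for residents at 6 and 9 months post-randomization". If the mask fails: "If unblinding happens by accident, then this will be reported to the CI". On learning from it: "The feasibility and effectiveness of this approach will be considered in the design of the future planned RCT". No other data item on masking is named, and nothing says when removed items go back.

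Three other sections bear on this:

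- Use of COG-D in daily care practice puts unlabelled Daisies where they are most useful, with residents' rooms as the example, and labelled ones in care plans. It adds: "Larger posters of the Cognitive Daisy (not resident-specific version) will be displayed in dining areas and in communal spaces".
- Feasibility outcomes counts "use and display of Daisies and revisions to care-plan based on COG-D assessments" towards acceptability, fidelity and adherence.
- COG-D intervention starts training and assessments straight after randomization. Six months of daily use follow.

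**The concern.** The resident candidate outcomes are proxy ratings that staff give in interviews with researchers. Staff in intervention homes may themselves use the Daisies, so the masked interviewer is the main safeguard against biased ratings. Whether that safeguard can be kept up in care homes is a fair question for a feasibility trial, and the article says it will consider it.

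The named data do not answer that question well. A report of accidental unblinding captures an event that someone notices and regards as reportable. A researcher who gradually infers the arm from a remark, a wall display or an informant's vocabulary may never file one. A low count then has two readings, that the mask held or that it failed quietly, and the data cannot separate them. The definitive trial could adopt an approach that does not work.

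The step also touches the intervention. Daisies are named among the items to clear, and their display is one of the things by which adherence is evaluated.

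**Working it through.** No figure in the article is in dispute. The check compares sections and sizes the problem.

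**1. Aim against data (Assignment of intervention).** Aim: consider how workable and effective the masking approach was. Data named: accidental unblindings reported to the CI. No record of the masked researcher's belief, no criterion and no denominator is given.

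**2. What a count of zero would show.** Illustration, assuming one yes/no record per home, independent homes and every unblinding reported. With zero events in n homes the one-sided 95% upper bound is 1 − 0.05^(1/n).

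- n = 8: 31%
- n = 10: 26%
- intervention homes only, n = 4 to 5: 53% to 45%

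If only a fraction s of unblindings is reported, the bound on the true rate is the bound above divided by s. The article gives no s. Assuming s = 0.75, it is 0.312/0.75 = 42% for 8 homes and 0.259/0.75 = 35% for 10. Assuming s = 0.5, it is 62% and 52%.

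**3. Timing of the removal rule (COG-D intervention; Assignment of intervention).** Let Phase 1 (training and assessments) last t months from randomization. Daily use then runs from month t to month t + 6. For any t above 0, the 6-month visit falls inside it. The 9-month visit does so only if t exceeds 3, and t is not given.

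**4. Overlap with the adherence measure.** What is cleared: Daisies, posters and leaflets, in interview areas only. What counts towards adherence: display of Daisies. The common item is a Daisy hanging in an interview area. The overlap affects the measure if Daisies hang in those areas or display is scored around the visits. The article settles neither.

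**5. Size of one unmasking.** Randomization is by home.

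- Share of homes: 1/10 = 10% to 1/8 = 12.5%.
- Residents retained after the planned 30% loss (Sample size): 100 × 0.70 = 70, so 70/10 = 7 to 70/8 = 8.75 per home. At 6 months the number may be somewhat higher if losses come late.

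**6. What believed-arm records could show.** Visits: 8 × 2 = 16 to 10 × 2 = 20. Taking one guess per home, with chance 1/2 of being right, 7 or more correct of 8 has probability 9/256 = 0.035, and 9 or more of 10 has 11/1024 = 0.011. But 6 or more of 8 has 37/256 = 0.14. Only near-perfect guessing stands out, so these records describe and do not test.

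**The case against.** **The article is a condensation.** A masking form may sit in the full protocol, and nothing in the text confines reporting to one kind of event, so an inferred arm could be reported. Both points are fair, and it would be too strong to say that accidents are the only evidence there will be or that inference leaves no trace. What stands is that the article states an aim and names one data item for it, and that item can miss the failure most likely to go unnoticed.

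**Removal does not show that adherence is understated.** A reader might infer that the trial takes down what it scores. The text does not go that far. Removal is confined to interview areas, residents' rooms are the example location for Daisies, and the posters are generic and not part of the adherence measure. Fidelity and adherence are also followed through huddles, drop-in sessions and focus groups (Intervention fidelity and adherence).

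**One-sided removal does not by itself reveal the arm.** A reader might infer that leaflets left up in control homes and cleared in intervention homes would give the allocation away. The recruitment text, "Short information leaflets about the study will be circulated and placed at convenient locations in the care home", has no restriction by arm. But control homes may not implement COG-D (Usual care) and have no Daisies or COG-D posters to clear, and nothing says that recruitment leaflets or newsletters are still on show at 6 or 9 months. This route is speculative.

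**The gain is limited.** Masking the interviewer does nothing about informants who know their arm, and a neutral room largely achieves what the removal rule already seeks. This is true. The neutral room's advantage is that it leaves the displays alone and treats both arms alike.

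**Conclusion.** The point holds in a limited form. The plan means to learn whether its masking approach works and names only accident reports as data, so few or no reports could be misread as success. Separately, the removal rule may overlap with Daisy display as an adherence measure during the daily-use phase. That part is conditional on where Daisies hang and when display is scored, so the sections on removal, display and adherence should be reconciled.

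Each unmasking would affect one cluster, 10% to 12.5% of homes and about 7 to 9 residents at follow-up. The 10 to 13 residents per home in Study setting is a recruitment figure, and carrying it to the follow-up visits would ignore the planned loss. This sizing assumes 8 to 10 homes of equal size, 100 residents recruited and 30% lost. If the full protocol already holds a believed-arm record and a display schedule, the article needs only a sentence to say so.

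**What to change.** 1. At the end of each 6- and 9-month home visit, the masked researcher records the believed arm (COG-D, control, do not know), the cue, and when in the visits it arose. Report this descriptively by arm, beside the accident reports. The cue matters because a correct belief may come from a lucky guess or from apparent benefit, and not from a breach.
2. Replace the removal request with one instruction to both arms: hold proxy interviews in a room without study material, or by phone or video, and leave displays where they are. Use the same options in both arms, so that interview mode does not differ by arm.
3. Have an unblinded researcher record Daisy display on dates away from these visits, and state those dates.

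The cost is a change of wording under Assignment of intervention and Feasibility outcomes, 16 to 20 three-item forms, and finding a neutral room or arranging a call. With 8 to 10 homes the believed-arm data should not be tested formally.
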